### Patient follow-up and compliance

Follow-up measurements will take place combined with evaluation group meetings.

For patients in both groups, follow-up visits to the physician, diabetes nurse and dietician are registered.

A common limitation of weight loss studies is a selective loss to follow-up: higher drop-out rates occur among patients, who do not achieve their weight loss goals. We want to tackle this problem by use of incentives to keep all patients in the trial: motivating phone calls of the researcher, little gifts during the program, etc.

Further more, we will perform a follow-up and analysis of the drop-outs after completion of the study and compare completers and drop-outs at base-line. For this purpose, the drop-outs will be interviewed by a medical student, who is not involved in the study.

Compliance to the intervention is assessed by registration of the attendance to the CPI sessions: participants are considered non-compliant when they are absent on more then 8 sessions. Since we expect that the treatment will be less effective when more then 8 sessions are missed, this non-compliant participants will be considered drop-outs.

We have conducted a pilot study to improve our research protocol. We will not perform interim analyses and we will not define stopping rules, since the intervention has no serious side-effects.

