## Methods/design

### Design of the study

This study is a randomized controlled parallel group intervention trial.

When patients lose equally or more than 5% of their bodyweight in the first 8 weeks of the VLCD, they are included in the intervention trial testing CPI. This arbitrary cut-off value was chosen because of its relatively large effect on the risk profile [3]. Moreover, we need a relevant weight loss to investigate weight maintenance after weight reduction. After randomization, stratified to the achieved weight loss at 8 weeks, participants are assigned to one of the following conditions:

1. VLCD + conventional treatment

2. VLCD + conventional treatment + CPI

The duration of the diet period will be 20 weeks: 8 weeks of VLCD (<800 kcal/day) followed by 12 weeks of slowly reintroducing a normal, mildly energy-restricted diet (1300 kcal/day). During week 10 of the diet, the intervention group starts with a total of 17 sessions of CPI. The first 10 sessions are weekly sessions; followed by two 2-weekly sessions, two monthly sessions, two 3-monthly sessions and 1 session with an interval of 6 months.

Outcome measurements are assessed at baseline, after finishing the intensive CPI-period at 4 months and subsequently at 1 year, 1,5 years and 2 years after randomization. At 8 weeks (randomization after VLCD), only the primary outcome (weight) will be measured.

Figure 1 shows the design of the study.

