#### Phase 1: control group

Following the VLCD-period and gradual reintroduction of normal diet, the control group receives usual care, provided by the diabetes team of the out-patient diabetes clinic of the Erasmus Medical Centre. Usual care consists of a 3-monthly visit to the physician and diabetes nurse, including medical examinations. Dietary treatment is part of usual care by referral to a specialized dietician. Patients are free to make additional appointments with their dietician in- or outside the hospital and they can choose to follow whatever diet they would like during the follow-up period. Both the number of visits to a dietician and the dieting methods, products and duration of the diet are noted during the follow-up period of 2 years. Dieticians in our hospital are all trained in motivational interviewing to motivate the patients in changing their lifestyle. All members of the diabetic team encourage the patients to get enough exercise, but we do not refer to an exercise programme. Patients in need of psychological help (ie psychological disorder, clinical depression, major eating disorder) are referred to a clinical psychologist in- or outside the hospital. In our population, these referrals are rare. Nonetheless, the number of visits to a psychologist as well as to other caregivers will be noted during this trial. CBT or techniques of PST and PC are no part of usual care.

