### Statistical analyses

All analyses will be conducted according to the intention-to-treat as well as the on-treatment principle. We consider participants on-treatment when they miss less then 8 sessions CPI.

At baseline, comparability between the control- and intervention group will be assessed to test the success of the randomization. As measures of central tendency for numerical data we will use the mean (in case of normal distribution) and median values (in case of non-normal distribution), with respectively the standard deviation and interquartile range as measures of dispersion.

Mixed modelling, also known as random effect modelling, multilevel or hierarchical linear regression analyses will be applied for longitudinal analyses of the data. Mixed modelling can efficiently handle data with missing and unbalanced time-points. It corrects for bias when absence of data is dependent on characteristics that are present in the models (missing at random, MAR) [62]. There will be two levels in the models. The patients constitute the upper level, their repeated measures the lower level. First, for each outcome variable a saturated model will be postulated, with the primary or secondary outcomes as dependent variables. The saturated models will include treatment group, time, quadratic time, logarithm of time and all treatment-time interactions as fixed effects. The deviance statistic [63] using restricted maximum likelihood [64] will be applied to determine the covariance structure. Next, using Wald tests, the saturated models will be reduced by eliminating insignificant fixed effects. The significance of the difference between the saturated models and the parsimonious final models will be determined with the deviance statistics using ordinary likelihood.

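### CPI patients who miss more than 8 sessions are classed as drop-outs, a label only one arm can receive and whose effect on the intention-to-treat analysis is left undefined

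*Protocol article*

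**What the plan says.** - **Rule.** Under Patient follow-up and compliance, "participants are considered non-compliant when they are absent on more then 8 sessions". The reason given is that the treatment is expected to work less well in them. The consequence is that "this non-compliant participants will be considered drop-outs".
- **Who can meet it.** Under Design of the study, "the intervention group starts with a total of 17 sessions of CPI". Under Phase 1: control group, "CBT or techniques of PST and PC are no part of usual care". No control patient can miss a CPI session.
- **Other uses of the term.** The same compliance section treats drop-out as selective loss to follow-up, noting that "higher drop-out rates occur among patients, who do not achieve their weight loss goals". It also aims to retain every patient. The follow-up and analysis it describes for drop-outs take place after the study has been completed. The sample size section uses the term for the 25% allowance that raises 52 per group to 140 in total.
- **Analysis sets.** Under Statistical analyses, "All analyses will be conducted according to the intention-to-treat as well as the on-treatment principle", followed by "We consider participants on-treatment when they miss less then 8 sessions CPI".

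**The concern.** Stopping therapy and leaving the trial are different events. A patient who no longer attends CPI can still be weighed at 1, 1.5 and 2 years, and an ITT analysis needs those weights. Giving non-attenders the label used for lost patients invites site staff and analysts to handle them as lost.

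Three features make this more than untidy wording. The label depends on behaviour after randomisation, it exists in one arm only, and the authors themselves expect attendance to matter for the effect. If later weights were not collected or not used, the CPI arm would be represented at 2 years mainly by its attenders, while the control arm kept everyone it could measure. The mixed model relies on missingness being explained by what is in the model. The fixed effects listed are treatment group, three functions of time and their interactions; attendance is not among them. Drop-out rates would also stop being comparable between arms. Weights that were never taken cannot be recovered by a later analysis plan.

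**Working it through.** **1. The stated sample size.** Inputs from Sample size calculation: mean 110 kg, SD 22 kg, difference 5%, baseline-end correlation 0.90, alpha 0.05 (taken as two-sided), power 0.80.
- Difference = 0.05 × 110 = 5.5 kg; 5.5/22 = 0.25, as stated.
- SD of change = 22 × √(2 × (1 − 0.90)) = 9.84 kg.
- n per group = 51 by the normal approximation. With the noncentral t, 51 gives 79.8% and 52 gives 80.6%, so 52 reproduces.
- 52/0.75 = 69.3, rounded up to 70 per group, or 140 in total. This also reproduces.

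**2. Who gets the label, and when.** More than 8 missed out of 17 means 9 or more missed. Attending all 10 weekly sessions leaves only 7 to miss, so at least 2 weekly sessions must be among the absences. The label can first apply at session 9. For a patient who misses 2 weekly sessions and all 7 relapse-prevention sessions, it applies only at session 17, which the Discussion places 1.5 years after randomisation.

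**3. The cut-offs side by side.**

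| Sessions missed | Compliance section | Statistical analyses |
|---|---|---|
| 0-7 | not non-compliant | on-treatment |
| 8 | not non-compliant | not on-treatment |
| 9-17 | non-compliant, drop-out | not on-treatment |

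A patient with exactly 8 absences is neither non-compliant nor on-treatment.

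**4. Illustration if the data were deleted.** Assumptions not in the article: a fraction p of the CPI arm is non-compliant, and r is the correlation between a normally distributed attendance tendency and weight change. Deleting the lowest p of attenders shifts the CPI mean by r × φ(z_p)/(1 − p) × 9.84 kg.
- p = 0.15: 0.2332/0.85 × 9.84 = 2.70. The shift is 0.54 kg (r = 0.2) to 1.08 kg (r = 0.4).
- p = 0.25: 0.3178/0.75 × 9.84 = 4.17. The shift is 0.83 kg to 1.67 kg.
- As a share of 5.5 kg: 0.54/5.5 = 10% to 1.67/5.5 = 30%.
- Type I error with 52 controls and 52 × (1 − p) CPI patients: 0.058 (0.54 kg, 44.2 CPI patients) to 0.126 (1.67 kg, 39 CPI patients), against a nominal 0.05.

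**5. Sensitivity to the assumptions.** Suppose instead that 10-30% are non-compliant and their weight change is 3-8 kg worse than that of attenders. The shift is then p × gap, from 0.1 × 3 = 0.3 kg to 0.3 × 8 = 2.4 kg. With 70 per group before deletion, type I error runs from 0.054 to 0.258. If attendance is unrelated to weight change, or the patients are kept with measured weights, the shift is zero.

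**6. Power.** If non-compliers came on top of the 25% loss, 70 × 0.75 = 52.5 controls would face 52.5 × 0.85 = 44.6 or 52.5 × 0.75 = 39.4 CPI patients. Power for 5.5 kg would be about 0.78 or 0.75-0.76. If all 70 per group are measured, it is 90.7%, before any dilution of the effect by non-attendance.

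**The case against.** A reader might infer that the rule removes non-attenders from the ITT analysis and so undoes it. The article does not support that. It plans ITT for every analysis, its statistical section ties the session count to the on-treatment set, and it nowhere says that weighing stops. The label may serve only that set and the comparison of completers with drop-outs. This stands: the effect on ITT is undefined rather than wrong.

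A reader might also infer that the authors expect non-attenders to be poor responders by nature. Their stated reason concerns the amount of treatment received. That such patients regain more weight is plausible, but it is an assumption.

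The figures in steps 4 and 5 describe deleting patients from a comparison of change scores. The planned mixed model would keep each patient's earlier weights. The 8-week weight always precedes the label, the 4-month visit falls near its earliest possible date, and late non-compliers would have further weights. Where earlier weights predict later ones, the bias would shrink. This also stands, so the figures are not estimates for the planned analysis.

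The power loss assumes that non-compliers come in addition to the 25%, which the article does not say.

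What the objection does not remove is that one word covers both non-adherence and loss to follow-up, that it is applied to one arm, and that the only follow-up described for this class comes after study completion.

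**Conclusion.** The concern holds in conditional form. The rule is one-sided and its consequence for ITT is not stated. If the label ends measurement or use of weights, it conflicts with the planned ITT analysis and with the aim of retaining every patient, and it can bias the primary 2-year contrast towards CPI. If the label is only a compliance category, there is no bias.

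The illustrative 0.5-1.7 kg (10-30% of the target difference) rests on outside assumptions and on outright deletion. It shows why the wording should be settled and does not predict the trial's result. The mismatch at exactly 8 missed sessions is a plain inconsistency that depends on no assumption. No stated sample-size figure is wrong.

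**What to change.** - Define stopping CPI and leaving the study as separate events. Keep drop-out for withdrawal from the study or lost contact.
- State that patients who miss sessions are still weighed at every study visit through 2 years and are analysed in the ITT model in the arm to which they were randomised.
- Use the session count only to define the on-treatment set.
- Reconcile the two cut-offs so that every number of missed sessions falls in a defined class.
- Optionally, for patients who stop study visits, use a routine-clinic weight near 2 years in a sensitivity analysis. The article says "Usual care consists of a 3-monthly visit to the physician and diabetes nurse, including medical examinations" but does not confirm that weight is recorded there. Such weights would not come from the blinded assistants and might be taken on a different scale, so they should not replace study weights.

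The cost is a few sentences of protocol and analysis text, plus the effort of recalling non-attenders for visits that are already scheduled. The sample size of 140 need not change.

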### Data/results pilot study

In order to test the protocol we conducted a pilot study, in which we included 13 patients to asses the study design and logistic pathways of the VLCD-period and the first 10 weeks of CPI. In this pilot study, we found that the protocol was feasible and that no major changes had to be done. The only change we made was in the lay-out of the questionnaires, making them better understandable to our participants. Results of this pilot study (baseline and T=4 months) are shown below (Table 4 and 5).

**Table 4 T4:** baseline characteristics pilot group

	**Baseline (n=13)**	
**Sex (%)**	Males	25%
	Females	75%
**Age (y)**		49.5
**Insulin dependant (%)**	Insulin dependant	75%
	Non-insulin dependant (OAD)	25%

**Table 5 T5:** Outcome measurements pilot group

	**Baseline (n=13)**	**T1 = 4 months (n=13)**	**95%CI**
**Weight (kg)**	114.8	106.0***	[5.2-12.4]
**Waist circumference (cm)**	121.4	113.7**	[3.2-12.2]
**Systolic BP (mmHg)**	144.6	127.9*	[1.1-32.2]
**Diastolic BP (mmHg)**	86.1	78.0	[−0.4-16.7]
**Total cholesterol (mmol/l)**	5.0	4.5	[−0.2-1.3]
**HDL cholesterol (mmol/l)**	1.7	1.3	[−0.3-1.3]
**LDL cholesterol (mmol/l)**	2.6	2.5	[−0.3-0.5]
**Triglycerides (mmol/l)**	3.6	2.6	[−1.1-3.0]
**HbA1c (mmol/mol)**	66.3	66.6	[−9.8-9.1]
**Insulin (IU)**	82.3	32.3*	[7.3-94.7]
**Depression score (HAD)**	5.7	4.6	[−1.5-3.7]
**>8 = (sub)clinical**			

Paired samples *T*-test *p<0.05 **p<0.01 ***p<0.001.

### Statistical analyses

All analyses will be conducted according to the intention-to-treat as well as the on-treatment principle. We consider participants on-treatment when they miss less then 8 sessions CPI.

At baseline, comparability between the control- and intervention group will be assessed to test the success of the randomization. As measures of central tendency for numerical data we will use the mean (in case of normal distribution) and median values (in case of non-normal distribution), with respectively the standard deviation and interquartile range as measures of dispersion.

Mixed modelling, also known as random effect modelling, multilevel or hierarchical linear regression analyses will be applied for longitudinal analyses of the data. Mixed modelling can efficiently handle data with missing and unbalanced time-points. It corrects for bias when absence of data is dependent on characteristics that are present in the models (missing at random, MAR) [62]. There will be two levels in the models. The patients constitute the upper level, their repeated measures the lower level. First, for each outcome variable a saturated model will be postulated, with the primary or secondary outcomes as dependent variables. The saturated models will include treatment group, time, quadratic time, logarithm of time and all treatment-time interactions as fixed effects. The deviance statistic [63] using restricted maximum likelihood [64] will be applied to determine the covariance structure. Next, using Wald tests, the saturated models will be reduced by eliminating insignificant fixed effects. The significance of the difference between the saturated models and the parsimonious final models will be determined with the deviance statistics using ordinary likelihood.

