## Background

Diabetes has become a worldwide epidemic: the estimated global prevalence was 2,8% in 2000 and is expected to rise up to 4,4% in 2030. In the year 2000 the excess global mortality attributable to diabetes was 5,2% making diabetes the fifth leading cause of death [1]. The increase in prevalence is associated with aging of the population, the increasing prevalence of obesity in combination with physical inactivity. Cardiovascular disease is the major cause of death among patients with diabetes. An intensive pharmaceutical and behavioral therapy treatment has been estimated to reduce the risk of cardiovascular and micro vascular events by approximately 50% [2].

Approximately 80% of the people with type 2 diabetes are overweight. Losing weight is the cornerstone of prevention and treatment of type 2 diabetes: it decreases the resistance to insulin, improves glycaemic control and reduces hypertension and lipid abnormalities [3-5]. Weight loss interventions thus may contribute to a reduction of cardiovascular risk and is shown to reduce mortality in patients with type 2 diabetes and obesity [6].

Unfortunately, interventions aimed at weight reduction have only a limited effect in the long run because of regain of the initial weight loss. The required long-term lifestyle change seems difficult to achieve [7]. A meta-analysis of weight loss interventions in adults with type 2 diabetes showed that multi-component interventions including Very Low Calorie Diets may hold promise for achieving weight loss [7,8]. However, trials with long follow-up periods are lacking and the most effective type of psychological intervention remains unclear.

In the present study, we determine the effect of an integrated multi-model cognitive group therapy, in obtaining and maintaining favourable effects on weight and cardiovascular risk profile during 2 years of follow-up after a Very Low Calorie Diet.

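### Secondary-outcome models omit weight, which the plan expects to drive drop-out; the likely bias is modest and the weights already collected can address it

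*Protocol article*

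**What the plan says.** Four statements in the protocol article bear on this point.

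- **Condition.** Statistical analyses says of mixed modelling: "It corrects for bias when absence of data is dependent on characteristics that are present in the models (missing at random, MAR".
- **Expected driver.** Patient follow-up and compliance describes selective loss to follow-up as a common limitation of weight-loss studies: "higher drop-out rates occur among patients, who do not achieve their weight loss goals". The sample size section allows for 25% drop-out.
- **Model content.** Statistical analyses plans one model per outcome ("for each outcome variable a saturated model will be postulated, with the primary or secondary outcomes as dependent variables") with the same terms each time: "The saturated models will include treatment group, time, quadratic time, logarithm of time and all treatment-time interactions as fixed effects". After that, "the saturated models will be reduced by eliminating insignificant fixed effects".
- **Data available.** Design of the study states: "At 8 weeks (randomization after VLCD), only the primary outcome (weight) will be measured". Secondary outcomes are measured before the diet and then from 4 months.

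Against selective drop-out the article plans retention incentives, interviews of drop-outs, and an analysis to "compare completers and drop-outs at base-line".

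**The concern.** Weight is in the model only when weight, or a measure that largely carries it such as BMI or waist, is the outcome. The primary analysis meets the plan's condition through the patient's own weight record. A model for HbA1c or blood pressure sees the arm, the time and that outcome's own past. Reduction only removes terms, so weight cannot enter later.

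The Background links weight loss to several secondary outcomes: "it decreases the resistance to insulin, improves glycaemic control and reduces hypertension and lipid abnormalities". If patients who regain weight leave, and their later HbA1c would have been worse than their earlier HbA1c suggests, the outcome-only model fills the gap too favourably. Where usual care loses more such patients, the CPI effect is understated. The courses within each arm are biased too. The secondary objectives on glycaemic control and cardiovascular risk rest on these models.

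The 8-week visit shows the gap most clearly. A patient lost before 4 months brings only a pre-diet value to every secondary model, although that patient's 8-week weight is on file.

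**Working it through.** **When omission matters.** Suppose drop-out before visit k depends on earlier weights. The model for outcome Y is then free of bias from this source if Y at visit k is independent of earlier weight, given arm and Y's own earlier values. Omitting weight matters only to the extent that weight predicts later Y beyond Y's own history.

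**Plan's figures, reproduced.**
- Weight difference: 5% × 110 kg = 5.5 kg; 5.5/22 = 0.25 SD.
- SD of weight change: 22 × √(2 × (1 − 0.90)) = 9.84 kg.
- Patients per arm: 2 × (1.96 + 0.84)² × 9.84²/5.5² = 50.2, so 51 by the normal approximation; 52 by the t test, as stated.
- With 25% drop-out: 104/0.75 = 138.7, so 139; the plan rounds to 140.
- HbA1c in Table 2: 0.25 × 12 = 3 mmol/mol. The implied standard error is 3/2.80 = 1.07 mmol/mol.

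**Assumptions not in the documents.** The weight–HbA1c correlation, the steepness of drop-out on weight, and whether HbA1c follows weight at once or with a lag. Drop-out, about 25% overall, depends on weight at the last attended visit and starts only after 4 months.

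**Same drop-out rule in both arms.** The main grid used 150,000 patients per arm, a true HbA1c difference of 3 mmol/mol, and a 5.5 kg weight difference from 4 months. The log-odds of drop-out were 1 or 3 per 9.84 kg, which are odds ratios per 8 kg of exp(8/9.84) = 2.3 and exp(3 × 8/9.84) = 11.5. The same rule gives 30% versus 20% drop-out (usual care versus CPI) at the lower slope and 35% versus 15% at the higher, because usual care is heavier.

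| HbA1c process | Correlation | Log-odds | Bias of contrast, outcome-only model (mmol/mol) | Share of 3 |
|---|---|---|---|---|
| Own history carries all weight information | 0.3–0.9 | 1 or 3 | −0.02 to 0.01 | about 0 |
| Visit-to-visit noise, no lag | 0.3–0.9 | 1 or 3 | 0.02 to 0.26 | 1–9% |
| Lagged response to weight | 0.3–0.8 | 1 | 0.05 to 0.16 | 2–5% |
| Lagged response to weight | 0.3 | 3 | 0.20 to 0.23 | 7–8% |
| Lagged response to weight | 0.6–0.8 | 3 | 0.42 to 0.65 | 14–22% |

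Positive bias is towards no effect, since the true difference is −3. With weight modelled jointly, the bias was within 0.02 in every cell. Within one arm the outcome-only bias reached 1.1 mmol/mol, in the most extreme cell.

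**Other parameter sets, correlation 0.3–0.5.** With an equal mechanism, shrinkage of the HbA1c contrast was 2–4%, 2–9% and 5–10% in three sets. With drop-out following weight only or mainly in usual care, it was 11–19%, 12–27% and 20–38%. One case of the latter kind (correlation 0.3, odds ratio 3 per 8 kg): true −2.03, outcome-only −1.54, joint −2.04, a shrinkage of 0.49/2.03 = 24%. Using the weight history removed the bias, and at 70 patients per arm it left the root mean squared error essentially unchanged.

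**Against sampling error.** On a contrast of 2.03, 2–9% is 0.04–0.18 mmol/mol, or 0.04–0.17 standard errors. Ten per cent of 3 is 0.30, or 0.28 standard errors.

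**Not covered.** Loss before 4 months was not simulated, and no outcome other than HbA1c was.

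**The case against.** The statement about missing at random is correct as a conditional, and the article does not claim that the condition holds for every secondary outcome. Modelling each outcome on its own history is ordinary practice, and auxiliary variables are often left to an analysis plan. This stands in part. But the article itself sets out the terms and the elimination-only reduction, and it offers the condition as a reason for the method, so the mismatch lies within its own text.

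The sentence on drop-out concerns weight-loss studies in general, and patients who miss the 5% goal leave before randomisation. Applying it to later regain is an inference, though a natural one, since the article gives it as the reason for its retention incentives.

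The 25% is not purely missing data. CPI patients absent from more than 8 sessions also count as drop-outs and may still be measured. This stands: the amount of missing data may be smaller than simulated.

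The HbA1c link may be weak. In the pilot, mean weight fell by 114.8 − 106.0 = 8.8 kg while HbA1c went from 66.3 to 66.6, and medication is adjusted during the diet. This cuts both ways: a weak link limits the bias, but it also makes HbA1c history a poor stand-in for weight. Group means from 13 patients settle neither.

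A reader might infer that the CPI effect will be shrunk by a quarter or more. That needs weight-driven drop-out mainly in usual care, or a very steep drop-out rule. The documents suggest neither, and Limitations expects the incentives to act alike in both arms.

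**Conclusion.** The point holds in a limited form. For HbA1c, blood pressure, lipids and insulin, the plan's own condition for bias correction is met only as far as each outcome's history carries the weight information. The likely bias in the HbA1c contrast is roughly 0–10% under an equal mechanism with moderate assumptions, towards no effect, and small against the standard error. It reached 22% only where a lagged correlation of 0.8 met a drop-out odds ratio of 11.5 per 8 kg. All sizes rest on assumed correlations and drop-out slopes.

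A reader might also infer that the condition fails outright for every secondary outcome, HADS and EQ-5D included. The documents do not support this. The Discussion ties depression and anxiety to weight only indirectly, as possible determinants of weight maintenance, and no link is stated for EQ-5D, so the consequence there is uncertain. The primary weight analysis is not affected. This is a worthwhile, cheap improvement, not a defect that invalidates the secondary results.

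**What to change.** In Statistical analyses, add wording such as: 'Missing secondary outcomes will be multiply imputed separately by arm, with all recorded weights, including the 8-week weight, as auxiliary variables; the mixed model described above will then be fitted to the imputed data. Where it converges, a bivariate mixed model with weight may be used instead. Weight after randomisation will not be entered as an ordinary covariate.'

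The last sentence is needed because the Discussion expects maintained weight loss to bring the gains in glycaemic control and cardiovascular risk. Adjusting for it would change the treatment effect being estimated.

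The cost is somewhat more programming and model complexity. Imputation is the safer default, since bivariate models for many outcomes in about 140 patients may not all converge. No new data, visits or patients are needed.
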